### Randomization and blinding process

A researcher specially trained will be responsible only for recruiting the participants to enter the study and will give them all the information about the study, obtain your consent through Google Forms.

An assistant researcher not involved with the recruitment, intervention, and assessment will generate the allocation sequence. The participants will be allocated to the following groups: A—intervention, an educational program of telerehabilitation and PFMT practice and B—control, who will be invited to maintain their routine activities. Randomization will be carried out via website (http://www.randomization.com) using a computational list of random numbers and will be concealed (by means of a sealed brown envelope).

Participants’ data will be kept only with the assistant researcher not involved with other parts of the research process to process to protect confidentiality before, during, after the intervention, and during data analysis. The trial is assessor-blinded in relation to the allocation of the participants.

The senior researcher who is not involved with the recruitment, intervention delivery, and assessment will have access to the trial data. We have planned to submit the manuscript to an open access journal that make all data available to readers as an appendix or under request.

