## Methods

### Study design

Randomized and controlled, two-arm blinded evaluator clinical trial was designed to evaluate the effect of a telerehabilitation program in women undergoing clinical practice of radiotherapy and brachytherapy of gynecological pelvic cancer on the primary outcome of the prevalence of reports of UI, which will be evaluated using the following question from the International Consultation on Incontinence Questionnaire—Short Form (ICIQ-SF) “how often do you lose urine?”.

Secondary outcomes will be the severity and impact of UI on quality of life, sexual function, FI, self-esteem, quality of life, location and perception of pain intensity, presence and intensity of dyspareunia, vaginal stenosis, and physical activity levels. Finally, the intervention group will respond about treatment satisfaction, adherence to supervised sessions, home guidance through home diary recording, recording of adverse effects, and System Usability Scale.

Participants will be randomized to an intervention group that will participate in a telerehabilitation program or control group. This protocol will be reported according to the Protocol Items Standard: Recommendations for Intervention Trials checklist (SPIRIT) 2013: items recommended for a clinical trial protocol and related documents. It is a superiority trial.

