Participants will fill out a diary about their adherence to PFMT, and there will be a place where they will be asked about any side effects or discomfort related to the intervention. At the last assessment, they are asked again about any unintended effects related to the experimental intervention. The type and number of undesirable effects will be reported in full as an important outcome of the trial. Although adverse effects from these types of interventions are not very common or serious, all participants are assured that they can discontinue their participation at any time for any reason, including any adverse effects.

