##### Adherence to supervised sessions and recording of adverse effects

A record will be made by the main researcher during the intervention regarding adherence to supervised sessions, as well as adverse effects during the intervention through a diary record.

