### Data collection

Data collection will be previously scheduled with participants online via Google Meet. The questionnaires will be applied in an interview format and will last 60 min; a researcher will receive training beforehand for data collection and will not participate in the intervention. The questionnaire covers general and clinical information, UI, sexual function, self-esteem, pain, dyspareunia, FI, and quality of life. All data collection will take place in two moments, firstly, in the period before the start of the intervention, called baseline (T0), and at the moment after the first stage of the intervention, that is, after the initial 12 weeks (T1) (Fig. 1).

Data collection from the control group will be carried out using the same questionnaires applied to the intervention group. Collection will be scheduled with the participants and will take place at the same interval as the intervention group.

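### Intervention-only items sit at the same T1 assessment as the blinded outcomes, so assessor blinding is unprotected, and adverse effects have no control comparison

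*Protocol article*

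**What the plan says.** **Blinding.** Randomization and blinding process states: "The trial is assessor-blinded in relation to the allocation of the participants". Study design likewise describes a blinded evaluator.

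**How outcomes are collected.** Under Data collection, "The questionnaires will be applied in an interview format and will last 60 min". The interviewer is a trained researcher who takes no part in the intervention. All collection happens at T0 and T1.

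**Items for one arm.** Study design says "the intervention group will respond about treatment satisfaction, adherence to supervised sessions", then adds the home diary, "recording of adverse effects, and System Usability Scale". Table 2 ticks satisfaction and SUS at the post-intervention point only, in the same table as the outcome questionnaires. The Intervention section adds: "At the last assessment, they are asked again about any unintended effects related to the experimental intervention".

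**Adverse effects.** The Intervention section gives them weight: "The type and number of undesirable effects will be reported in full as an important outcome of the trial". The section on adherence and adverse effects says how they are captured: "A record will be made by the main researcher during the intervention regarding adherence to supervised sessions, as well as adverse effects". The main researcher is also the physiotherapist who delivers the programme.

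**Statements that pull the other way.** Data collection says controls are given the questionnaires used in the intervention group, at the same interval. Statistical analysis lists SUS among the scores for a linear mixed model with group, time and their interaction as fixed effects.

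**The concern.** Participants cannot be blinded to a 12-week programme of group meetings, and the outcomes are self-reported. A neutral interviewer is the only blinding claimed for outcome collection. If that interviewer also handles a form on satisfaction with the programme, or asks about effects of the intervention, the arm is disclosed. If this happens before the comparative outcomes are recorded, prompting and coding could differ by arm.

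The second stake is harms. An outcome described as important, but gathered in one arm, cannot support a comparison. The Background describes pelvic pain, vaginal stenosis and dyspareunia as consequences of the cancer treatment itself, so some complaints are expected without any programme.

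**Working it through.** No stated figure bears on this point, so the check is a cross-reading.

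**Step 1. What falls at T1, for whom, and who asks.**

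| Item | Arm | T0 | T1 | Mode or person stated |
|---|---|---|---|---|
| ICIQ-SF and other outcome questionnaires | both | yes | yes | interview, by a researcher outside the intervention |
| Treatment satisfaction | intervention (Study design) | no | yes | none |
| SUS | intervention (Study design) | no | yes | none |
| Question on effects of the intervention | intervention (by its content) | not applicable | yes | none |
| Adverse-effect record during the 12 weeks | intervention | not applicable | not applicable | main researcher, participant diary |

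The effects question belongs at T1 because it is put at the last assessment and there are only two. Interview is the only questionnaire mode the article states. Nowhere does it give the three arm-revealing items to another person, to another route, or to a place after the outcomes.

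**Step 2. Does giving controls the same questionnaires solve it?** Taken literally, this contradicts Study design. Nor would it protect blinding: a control participant asked to rate a system she never used, or her satisfaction with a programme she did not attend, would show her arm by her answer.

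**Step 3. SUS in the group-by-time model.** Two arms and two time points make 2 × 2 = 4 cells. The fixed part of the model has 4 parameters: intercept, group, time and interaction.
- On Study design and Table 2, SUS exists in 1 of the 4 cells (intervention, T1). One mean can be estimated; group, time and interaction cannot.
- If controls also answered at T1, 2 of the 4 cells would be filled. A group difference would be estimable, though it would mean nothing; time and interaction still would not.
- With one value per woman, the random individual effect cannot be separated from residual error.

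The model therefore cannot be fitted to SUS as described on either reading.

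**Step 4. Comparator for adverse effects.** The routes described are the intervention-group list in Study design, the exercise diary, the main researcher's record, and the T1 question about the intervention. All four cover the intervention arm only, and none yields a control count.

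**Step 5. What the both-arm scales cover.** Table 2 measures pain and its location, dyspareunia, fecal incontinence, stool consistency and vaginal stenosis in both arms at T0 and T1. Worsening in these domains can be compared. Complaints outside them cannot, nor can effects that arise and settle between the two assessments, which the diary and session record could catch in one arm only.

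**The case against.** **No section says the blinded interviewer gives these items.** This stands. The content list under Data collection names neither satisfaction, SUS nor adverse effects. It settles nothing, however, because it also leaves out stenosis, stool consistency and physical activity, which Table 2 schedules. SUS, with its optional essay question, and satisfaction, as a line between two anchors, would suit self-completion, but the article does not say they are self-completed.

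**The order may be harmless.** Table 2 lists ICIQ-SF first and satisfaction and SUS last. If that were the order of administration, the primary answer would be recorded before any revealing item. The table is not presented as an order, so this is possible but not established.

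**The main researcher records adverse effects.** That covers the intervention period, not the T1 question, satisfaction or SUS.

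**An article need not say who hands over each form.** Fair as a general rule. The point here is not a missing detail: the article claims blinding beside a schedule that puts it at risk, and contradicts itself on what controls are asked.

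**The practical effect is small.** This largely stands. The primary item has six fixed categories and is answered by women who know their arm, so interviewer knowledge probably adds little.

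**Controls cannot report effects of a programme they did not receive.** True of that wording, but not of a neutral question on adverse events.

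Two stronger readings are tempting. A reader might infer that all 29 planned intervention-arm interviews reveal the allocation during outcome assessment. The article does not support this, since it states neither who asks nor in what order. A reader might also infer that harms in the intervention arm cannot be told from background symptoms at all. That goes too far, because several pelvic symptoms are measured in both arms.

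**Conclusion.** The point holds in two limited parts and should be addressed.

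1. **Blinding is claimed but not protected.** Arm-revealing items share T1 with the interview outcomes, with no stated separation. Whether the assessor would learn the arm, and when, is unknown. The article gives no basis for sizing the added bias. If present it would be expected to favour the intervention, but that is not shown, and it is probably limited. This rests on interview being the only stated mode and T1 being the last assessment. The passages on control-group questionnaires and on SUS in the mixed model contradict Study design whatever the answer on blinding.

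2. **Adverse effects have no control comparison.** This follows directly from the described collection routes and does not depend on who conducts the interview. The both-arm symptom scales reduce the gap but do not close it.

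Neither part affects the sample size or the definition of the primary outcome.

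**What to change.** - At T1, run the same blinded interview in both arms, with ICIQ-SF first.
- Collect SUS, satisfaction and intervention-specific effects afterwards, on a self-completed online form outside the assessor's view. The trial already uses Google Forms for consent.
- In the shared interview, ask both arms one identical, neutrally worded adverse-event question and report the answers by arm. Keep the diary and session record as descriptive intervention-arm data.
- Reconcile Study design, Data collection and Statistical analysis: state which questionnaires controls receive, remove SUS from the group-by-time model, and describe it in the intervention arm only.

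Cost: one short online form, one more interview question and a few edited sentences. A few women may not return the form, which would leave some SUS and satisfaction data missing but would not touch the comparative outcomes.

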### Intervention

Participants allocated to the intervention group will participate in an educational program, consisting of 12 consecutive 90-min meetings offered once a week for 12 weeks, which will be held virtually via Google Meet. The intervention will be conducted by a physiotherapist with 23 years of training and who is the main researcher.

The telerehabilitation program will include lectures on the anatomy, functions, and dysfunctions of the PF muscle, risk factors for the development of disorders, therapeutic options, and preventive measures, with a strong focus on the PF muscle through exercises and awareness of the function of the PF muscle during different tasks of daily life that increases intra-abdominal pressure, such as coughing, sneezing, and other activities and urinary urgency.

To carry out the didactic activities, illustrative figures from the PFMT will be used. The lectures will include topics such as gynecological pelvic cancer, physical activity and cancer, UI, continence mechanism, vaginal stenosis, sexual dysfunction, dyspareunia, FI, and sexual dysfunctions after treatment for gynecological pelvic cancer, and all meetings will have a practical part with supervised PFMT. After the lectures are finished, the material used in the lectures will be sent by e-mail.

The intervention protocol is described in detail in Table 1, and Table 1 contains the PFMT progressions. A record of adherence to supervised sessions will be made, as well as a record of adverse effects during the 12 weeks of intervention.

**Table 1 Tab1:** PFMT progression parameters

Sustained contractions															
**Week**	**No. of series**		**Repetitions**			**Contraction holding time**						**Relaxation time**			
1	2		6			4 s						4 s			
2	2		8			4 s						6 s			
3	2		10			5 s						8 s			
4	2		10			5 s						10 s			
5	2		10			6 s						10 s			
6	1		10			6 s						10 s			
7	1		10			7 s						10 s			
8	1		10			8 s						10 s			
9	1		10			9 s						10 s			
10	1		10			10 s						10 s			
11	1		10			10 s						10 s			
12	1		10			10 s						10 s			
**Fast contractions**															
**Week**		1		2	3	4	5	6	7	8	9		10	11	12
**No. of repetitions**		6 ×		6 ×	6 ×	10 ×	10 ×	10 ×	15 ×	15 ×	15 ×		20 ×	20 ×	20 ×

Progression of the 12 weeks of PFMT

**Frame 1** Roadmap for carrying out educational activities

**Table Taba:** 

1st meeting	Presentation of the team, justification for the group’s existence, and proposals regarding the health of women with gynecological pelvic cancer; What will be covered in the group; Explain the anatomy and physiology of the PF and genitourinary system: use of figures and computer-animated models; explanation about the stop test that will be carried out at home Stop test; Dynamics for body self-knowledge: activity on how to contract the PF, abdominal breathing technique for relaxation; Practice PFMT in the four positions sitting: lying down, four supports, sitting, and standing
2nd meeting	Physical activity and cancer; guidelines; aerobic and resistive exercises; authorization from the doctor to practice physical activity; Physical activity after gynecological pelvic cancer treatment; Benefits of physical activity in PF; Care; Stretching exercises Practice PFMT in the four positions sitting: lying down, four supports, sitting, and standing
3rd meeting	Gynecological pelvic cancer (types and etiology) Risk factors; Treatment; PF dysfunctions after cancer treatment; Physiotherapy; PF awareness, proprioception, and contraction exercise; Practice PFMT in the four positions sitting: lying down, four supports, sitting, and standing Practice breathing;
4th meeting	Impact of UI on quality of life; UI types; Explanation about PFMT and “the Knack” Practice PFMT in the four positions sitting: lying down, four supports, sitting, and standing
5th meeting	Continence mechanisms; Risk factors for UI in women and after treatment for gynecological pelvic cancer; Problem prevention: importance of prevention due to high prevalence; PF exercises, proprioception and contraction exercises; Practice PFMT in the four positions sitting: lying down, four supports, sitting, and standing; Practice breathing
6th meeting	Exams and possible treatments for UI; Role of physiotherapy in the process of comprehensive health: techniques and devices; Stretching exercises Practice PFMT in the four positions sitting: lying down, four supports, sitting, and standing
7th meeting	Vaginal stenosis after gynecological pelvic cancer treatment; Impact of vaginal stenosis on quality of life; Impact of sexual dysfunction vaginal stenosis; Treatment and encouragement of the use of vaginal dilators; Perineal massage; Practice PFMT in the four positions sitting: lying down, four supports, sitting, and standing; Practice breathing
8th meeting	Sexual dysfunction after gynecological pelvic cancer treatment; Dyspareunia; Impact of sexual dysfunction on quality of life; Practice PFMT in the four positions sitting: lying down, four supports, sitting, and standing
9th meeting	Fecal incontinence after treatment for gynecological pelvic cancer; Impact of anal incontinence on quality of life; Abdominal massage; Practice PFMT in the four positions sitting: lying down, four supports, sitting, and standing; Practice pelvic mobility exercises
10th meeting	Self-care in women’s health; Practice PFMT in the four positions sitting: lying down, four supports, sitting, and standing; Practice breathing
11th meeting	Resumption of main concepts; Practice PFMT in the four positions sitting: lying down, four supports, sitting, and standing;
12th meeting	Free; Practice PFMT sitting, standing, performing squats, bridges, and walking. Dance for pelvic mobility

Description of the stages of the 12 meetings

A Whatsapp group will be created with the participants and the main researcher as a way of welcoming the project, monitoring, and encouraging these participants to carry out PFMT at home, use vaginal dilators, and practice physical activity. In infographic 1, examples of the folder will be sent to the participants one times a week.

**Infográfico 1:** Folders will be sent to participants throughout the 12 weeks.
[figure not shown]

During the 12 weeks of the study, participants will be monitored on their adherence to perform the PFMT at home. They will complete a daily record booklet on how many contractions they performed, ranging from less than 10 contractions per day, from 10 to 20 contractions per day, from 20 to 30 contractions per day, from 30 to 40 contractions per day, and more than 40 contractions per day. Consequently, how many times a day, the contractions will take place, one time, two times, three times, or more than three times a day, as well as the positions in which the contractions will take place lying down, sitting, on all fours, and standing. In infographic 2, it shows how it will constitute the primer.

**Infographic 2:** Booklet for daily recording of the PFMT.
[figure not shown]

Participants will fill out a diary about their adherence to PFMT, and there will be a place where they will be asked about any side effects or discomfort related to the intervention. At the last assessment, they are asked again about any unintended effects related to the experimental intervention. The type and number of undesirable effects will be reported in full as an important outcome of the trial. Although adverse effects from these types of interventions are not very common or serious, all participants are assured that they can discontinue their participation at any time for any reason, including any adverse effects.

### Group control

Participants in the CG will be invited to maintain their routine activities and will have the opportunity to participate in the telerehabilitation program after the 12 weeks that served as control, in a second moment that will not be for research purposes, since the results could be influenced by previous assessments and reassessments.

### Assessment

#### Primary outcome measures

The primary objective of this study will be to evaluate the impact of a PF telerehabilitation program on the prevalence of reports of UI in participants post-radiation therapy treatment for gynecological pelvic cancer. UI is the primary outcome at all times of the study, that is, baseline and after 12 weeks of intervention. Therefore, could the intervention of an educational telerehabilitation program promote improvements in reports of UI in these participants?

The prevalence of UI will be assessed using the following question from the International Consultation on Incontinence Questionnaire—Short Form (ICIQ-SF). “How often do you lose urine” being 0—never, 1—once a week or less, 2—two or three times a week, 3—once a day, 4—several times a day, and 5—how long all.

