**Methods:**

Two-arm randomized clinical trial: an intervention group (IG) will evaluate the effect of a telerehabilitation program on women undergoing clinical practice of radiotherapy for the treatment of gynecological pelvic cancer and a control group (CG) will maintain the routine. Primary outcome is the prevalence of reports of UI, which will be assessed using the International Consultation on Incontinence Questionnaire—Short Form (ICIQ-SF). The secondary outcomes will be the severity and impact of UI on quality of life, location and perception of pain intensity, presence and intensity of dyspareunia, vaginal stenosis, fecal incontinence (FI), and levels of physical activity. Statistical analysis will be performed by intention-to-treat, and multivariate mixed effects analysis will be used to compare results.

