### Eligibility criteria

The study will consist of participants with UI after radiotherapy and/or brachytherapy for gynecological pelvic cancer who underwent treatment at the Oncological Research Center—CEPON in Florianópolis, Santa Catarina, Brazil.

Women are defined as inclusion criteria: age group over 18 years old; clinical stages I to III of gynecological pelvic cancer; having undergone surgery, radiotherapy, and/or brachytherapy; reporting stress UI, urgent UI, or mixed UI (self-reporting by the question Short Form (ICIQ-SF) “how often do you lose urine?”); do not have orthopedic or neurological limitations that prevent the practice of the telerehabilitation program; and not undergoing physiotherapeutic treatment.

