### Sample size

G*Power 3.1.9.2 software was used to calculate the sample size based on the difference between two means using the *T*-test, after a 12-week pilot study with 20 participants, 10 in the control group (CG) (2.8 ± 1.9) and 10 in the intervention group (IG) (1.41 ± 1.50). The variable considered for the calculation was the prevalence of UI through the ICQ (short-form) question “how often do you lose urine?” The answer is presented in the form of a Likert scale.

Taking these observations into account, a total number of 58 participants (29 IG and 29 CG) will be needed to detect a difference between the groups in the ICQ-SF question “how often do you lose urine?” after 12 weeks of intervention, assuming an alpha level of 0.05 and 80% power of the test.

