### Statistical analysis

Data will be de-identified, encoded, and stored in the database using the Excel Program. The software SPSS 22.0 will be used for the analysis of data. The description of quantitative variables will be expressed in mean, standard deviation, minimum value, median, and maximum value. Qualitative variables will be described in absolute and relative values (%). For all primary and secondary results, a 95% confidence interval and a significance level of 0.05 will be considered in the test. Both per-protocol and intention-to-treat analysis will be performed.

A linear mixed-effect model will be used to analyze the ICIQ-SF score, FSFI score, FIQL score, EORTC score, IPAQ score, ROSEMBERG score, and System Usability Scale. In the reassessment, individuals’ values will be considered random effects, and the groups, the times, and the interaction between them will be regarded as fixed effects. In addition, the McNemar test will verify changes in categories variables before and after the intervention. Both per-protocol analysis [21–23] and an intention-to-treat analysis will be also conducted. The Cohen effect size (*d*) will be calculated using the averages.

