#### Other outcome measures

##### The severity and impact of UI on quality of life

It will be assessed by the ICIQ-SF questionnaire; this questionnaire was translated into Brazilian Portuguese and culturally validated by Tamanini et al. [24] and consists of six questions with the aim of evaluating UI frequency, its perceived cause, severity, and its impact on quality of life. These will be measured using the total ICIQ-SF score (sum of questions one, two and three); the scores for this instrument range from 0 to 21 points, where higher scores indicate greater severity.

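### The primary outcome is called a prevalence of UI but is sized as the mean of a 0–5 frequency item, and no between-arm test is named for either

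*Protocol article*

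**What the plan says.** All references are to the protocol article.

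- **Name of the outcome.** The abstract's Methods states: "Primary outcome is the prevalence of reports of UI". The Primary outcome measures section gives the objective as "to evaluate the impact of a PF telerehabilitation program on the prevalence of reports of UI" and adds: "UI is the primary outcome at all times of the study, that is, baseline and after 12 weeks of intervention". The measure is one ICIQ-SF question on how often urine is lost, coded from 0 (never) to 5. No cut-off for UI present or absent is stated.
- **Sample size.** "The variable considered for the calculation was the prevalence of UI through the ICQ (short-form) question" is how the section describes its variable. Yet G*Power was used "to calculate the sample size based on the difference between two means using the" t-test, with 12-week pilot values of 2.8 ± 1.9 (control, n = 10) and 1.41 ± 1.50 (intervention, n = 10). The result is 58 participants, 29 per arm, at alpha 0.05 and 80% power.
- **Analysis.** "A linear mixed-effect model will be used to analyze the ICIQ-SF score, FSFI score" and further questionnaire scores, with group, time and their interaction as fixed effects. McNemar's test is assigned to before-and-after changes in categorical variables.
- **Meaning of ICIQ-SF score.** Under Other outcome measures, on severity and impact of UI: "These will be measured using the total ICIQ-SF score (sum of questions one, two and three"), range 0 to 21.
- **Entry.** Eligibility criteria: "The study will consist of participants with UI after radiotherapy and/or brachytherapy for gynecological pelvic cancer".

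**The concern.** A prevalence is a proportion; 2.8 and 1.41 are means of a graded item. The Sample size section uses the first name for the second quantity, and the Statistical analysis section lists neither. Study design declares a superiority trial, so the primary outcome needs a comparison between arms.

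The two readings can disagree. A woman who moves from leaking several times a day (4) to once a week or less (1) improves by 3 points on the item and still counts as incontinent. An intervention that makes leakage rarer but seldom abolishes it could succeed on the mean and fail on prevalence. If the choice is left open until results are known, the main conclusion may depend on which reading is taken up.

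**Working it through.** **1. Which analysis reaches the primary outcome?**

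| Reading of the primary outcome | Between-arm analysis named | Power stated |
|---|---|---|
| Prevalence (any leakage against never) | None; McNemar compares before with after within a group | No |
| 0–5 frequency item, mean at 12 weeks | None by name; the model list gives the ICIQ-SF score, defined as the 0–21 total | Yes |

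McNemar would be uninformative on treatment here. UI is an entry condition, so everyone starts positive and change can go only one way, whether it comes from treatment or from time.

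**2. The plan's own sample size.** Inputs from Sample size; two-sided alpha is assumed because sidedness is not stated.

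- Difference = 2.8 − 1.41 = 1.39.
- Pooled SD = √[(1.9² + 1.5²)/2] = 1.712; d = 1.39/1.712 = 0.812.
- Normal approximation: n = 2(1.960 + 0.842)²/0.812² = 23.8, so 24 per arm. The noncentral t gives 24.8, so 25 per arm, 50 in total.
- Power at 29 per arm: noncentrality 0.812 × √(29/2) = 3.09, critical t on 56 df = 2.003, power 86%.

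The stated 58 is not reproduced exactly. An unstated Wilcoxon–Mann–Whitney option (minimum efficiency 0.864) would give 24.8/0.864 = 28.7, so 29 per arm. The gap is on the conservative side and is a separate matter. What counts here is that the inputs and the test are those of a comparison of means.

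**3. Do the pilot figures imply a prevalence?** Only within wide limits. Let P0 be the proportion scoring 0 (dry), and treat the pilot SDs as exact moments on the 0–5 scale.

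- Control: E[x²] = 2.8² + 1.9² = 11.45. Since (x−4)(x−5) is never negative on the integers and equals 20 at x = 0, P0 ≤ (11.45 − 9×2.8 + 20)/20 = 0.31. The lower limit is 0.
- Intervention: E[x²] = 1.41² + 1.50² = 4.238. From (x−3)(x−4), P0 ≤ (4.238 − 7×1.41 + 12)/12 = 0.53. From (1−x)(5−x), P0 ≥ (4.238 − 6×1.41 + 5)/5 = 0.16.

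**4. Power for prevalence at 29 per arm, two-sided 0.05.** The proportions below are assumptions; the article gives none.

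| Basis | Dry, intervention | Dry, control | Power |
|---|---|---|---|
| Rounded normal: Φ((0.5−1.41)/1.5), Φ((0.5−2.8)/1.9) | 27% | 11% | 22% (Fisher) to 33% (uncorrected chi-square) |
| Maximum-entropy distribution on 0–5 | 38% | 19% | 26% (Fisher) to 36% (normal approximation) |
| Feasible limits | 53% | 0% | above 99% |
| Feasible limits | 53% | 31% | about 29% (Fisher) |
| Feasible limits | 16% | 31% | effect reversed |

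If 10% of controls were dry, 80% power would need about 41% (chi-square) to 45% (Fisher) of the intervention arm dry.

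**The case against.** The best defence is that only the label is wrong. Study design, Sample size and Primary outcome measures all point to the same question, and the last of these gives its 0–5 coding. The sample size is for a between-group difference in that question after 12 weeks, and the article asks about improvement in reports of UI, which suits a graded score. Item, contrast and time point then agree, and the power matches. This stands: a flat statement that the primary outcome has no matching power would go too far. It does not rescue the word prevalence, and it does not put the item in the model list.

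It can also be said that the abstract promises a mixed-effects comparison, that the ICIQ-SF score might loosely include its first item, and that an article may leave the exact test to a fuller document. That softens the point but does not remove it, because the article itself defines the score as the total. A later document could name a test, but it would have to depart from either the prevalence label or the means-based sample size.

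Three stronger readings are tempting and are not supported:

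- **The 0–21 total as a rival primary outcome.** The article places it under Other outcome measures and lists severity and impact as secondary. At most two readings of one item compete.
- **Baseline as an endpoint.** The sentence on baseline and 12 weeks reads naturally as assessment times, in line with Table 2 and Data collection, and the model needs baseline values.
- **A firm figure for low power on prevalence.** The 22% to 36% rests on assumed distributions, and the pilot summaries allow far better and far worse.

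**Conclusion.** The concern holds in this form: the primary outcome is labelled a prevalence, sized as the mean of a 0–5 item, and named in no between-arm analysis under either reading. The contradiction is within the article's own text and does not depend on any modelled figure.

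On size: if the item mean is meant, 29 per arm gives about 86% power at the pilot inputs (two-sided t-test, no loss to follow-up), so the sample size is adequate on its own terms. If a prevalence is meant, power is unstated and cannot be determined from the pilot means and SDs. The two illustrative distributions suggest it would be low; the limits of what the pilot allows run from near-certain detection to a reversed effect.

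**What to change.** 1. State one primary endpoint: the ICIQ-SF frequency item (0–5) at 12 weeks (T1), the variable on which the sample size rests.
2. State its estimate: the between-arm difference at T1 adjusted for the baseline item, by intention-to-treat, with 95% CI.
3. Name the item, separately from the ICIQ-SF total, in the model list under Statistical analysis.
4. Make prevalence at T1 (any leakage against never) a secondary outcome, compared between arms as a risk difference with 95% CI, and state that the sample size was not based on it.
5. Keep baseline as an assessment time, and note that baseline prevalence is 100% in both arms by design and so is not an outcome.
6. Replace the word prevalence in the abstract, Study design, Sample size and Primary outcome measures wherever the graded item is meant.

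The cost is protocol and analysis-plan wording and a matching registry update, made before unblinding. No new data, visits or participants are needed.
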